## Abstract

**Background:**

In the educational sector job demands have intensified, while job resources remained the same. A prolonged disbalance between demands and resources contributes to lowered vitality and heightened need for recovery, eventually resulting in burnout, sickness absence and retention problems. Until now stress management interventions in education focused mostly on strengthening the individual capacity to cope with stress, instead of altering the sources of stress at work at the organizational level. These interventions have been only partly effective in influencing burnout and well-being. Therefore, the “Bottom-up Innovation” project tests a two-phased participatory, primary preventive organizational level intervention (i.e. a participatory action approach) that targets and engages all workers in the primary process of schools. It is hypothesized that participating in the project results in increased occupational self-efficacy and organizational efficacy. The central research question: is an organization focused stress management intervention based on participatory action effective in reducing the need for recovery and enhancing vitality in school employees in comparison to business as usual?

**Methods/Design:**

The study is designed as a controlled trial with mixed methods and three measurement moments: baseline (quantitative measures), six months and 18 months (quantitative and qualitative measures). At first follow-up short term effects of taking part in the needs assessment (phase 1) will be determined. At second follow-up the long term effects of taking part in the needs assessment will be determined as well as the effects of implemented tailored workplace solutions (phase 2). A process evaluation based on quantitative and qualitative data will shed light on whether, how and why the intervention (does not) work(s).

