## Methods/Design

A quasi-experimental field study is conducted to determine the effectiveness of the participatory action approach (phase 1: needs assessment) and tailored work-oriented solutions (phase 2: implementation plan), compared to business as usual. The study is designed as a controlled trial (CT) with mixed methods (quantitative and qualitative) and three measurement moments: T0 at baseline (quantitative measurement), T1 at six months (quantitative and qualitative measurement) and T2 at 18 months (quantitative and qualitative measurement) (Figure 2). A CT is necessary to control for random changes, although the researchers are well aware of the fact that they are conducting a *social* experiment and that causal relations are thus embedded in complex contexts [38]. Randomization to experimental group (intervention group) or control group is practically impossible in this project, as often in organizational level workplace interventions [38], due to the aspirations of participating schools. Both schools participate in the study because they aim to solve a problem or reach a goal within a specific department of the school. The experimental groups were thus selected by the schools. To reduce the negative impact of selection bias, the control groups are selected by the researchers according to the ‘general control’ matching principle (or: frequency distribution control) [48]. Matching criteria are: department size (at least 150 employees), mean age of employees, and type of work (i.e. teaching vocational students and not secondary school pupils). Since the assignment to groups was out of our control, we will examine in the analyses whether propensity score matching is necessary. By applying the statistical technique of propensity score matching, the effect of the intervention can be estimated accounted for covariates that predict receiving the intervention. This way we expect to nullify potential confounding bias [49].

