#### Study population

The intervention is applied to one department in both schools, another department in the same school is matched by the researchers as a control group. The target group of the project are teaching and non-teaching (i.e. educational and administrative support staff) employees in two vocational education institutions and their managers. Employees who work within the vocational institution, but do not teach at a secondary vocational level are excluded from the study population (e.g. teachers in general secondary education for adults). All participants are asked to sign an informed consent at baseline.

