#### Phase 2: Implementation

In the implementation phase of the participatory action approach, the management has to take the first step. With support of the Engine of Development, the management team decides on which work-oriented solutions will be implemented. The solutions can be either evidence-based (e.g. adjusting classroom schedules), or new, tailor-made and specific to the context (e.g. adjusting the physical layout of class rooms). In any case, the management team explains to the employees which work-oriented solutions are (not) implemented and to what end. Furthermore, the method prescribes that the management team equips the plan of action with an implementation plan comprising amongst others a timeframe, a budget and the allocation of roles (e.g. the Engine of Development’s role). If the management team wishes, the HM-facilitator will take up a role during the implementation phase, for example in monitoring the plan’s progress or coaching the management team.

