### Strengths and limitations of the intervention

Less than a quarter of the intervention studies focus on primary preventive interventions, as assessed in a recent meta-analysis on stress interventions [35]. Thus, a first strength of the current intervention is the aim to alter job stress at its core (primary prevention).

Second, by making use of the participatory action approach, stakeholders at all levels are involved - teachers in the first place. This ‘bottom-up’ involvement of all stakeholders likely contributes to commitment to the proposed solutions. Solutions that can count on both the management and the work floor’s commitment are more sustainable and thus more likely to have impact [37,40].

A third strength is that the intervention is conducted in the same way for both schools, but the tailored workplace solutions can differ. This way we can compare different solutions on similar outcomes, further contributing to evidence-based practice.

Fourth, the project requires close collaboration between the intervention provider (i.e. the facilitator) and the researcher. They have a different task to fulfill within the project: the facilitator needs to make the intervention work, the researcher needs to make the study design work. Inevitably, their world views (or: paradigms) will meet and, maybe clash. An issue is that the intervention provider works from a ‘practice-based evidence’ perspective, asking himself at every step: is it useful? Is it important? Is it valid? Whereas researchers aim to contribute to evidence-based practice and therefore ask themselves: is it valid? Is it important? Is it useful? [84]. Even though the differing paradigms and activities will probably make the project difficult from time to time, the primary interest of both intervention provider and researcher is eventually the same: working happier and healthier in vocational education.

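### At 18 months the two-arm design identifies only the effect of the whole two-phase programme, not separate effects of the needs assessment and of the implemented solutions

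*Protocol article*

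**What the plan says.** The Abstract (Methods/Design) assigns an aim to each follow-up. For T1: "At first follow-up short term effects of taking part in the needs assessment (phase 1) will be determined". For T2: "the long term effects of taking part in the needs assessment will be determined as well as the effects of implemented tailored workplace solutions". The main Methods/Design section gives the purpose of the study as "to determine the effectiveness of the participatory action approach (phase 1: needs assessment) and tailored work-oriented solutions (phase 2: implementation plan"), with business as usual as the comparator. The measurement moments after baseline are "T1 at six months (quantitative and qualitative measurement) and T2 at 18 months (quantitative and qualitative measurement").

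The Study population section assigns the programme to "one department in both schools, another department in the same school is matched by the researchers as a control group". Under Phase 2: Implementation, the same departments move on from the plan of action that phase 1 produced: "With support of the Engine of Development, the management team decides on which work-oriented solutions will be implemented".

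The Effect evaluation section plans baseline-corrected multilevel comparisons at T1 and T2 by initial assignment. It adds a per-protocol analysis of workers who report at least two of the three needs-assessment steps. It plans no separate coefficients for the two phases.

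The Discussion (Strengths and limitations of the intervention) notes that solutions may differ between the schools and counts this as a strength: "This way we can compare different solutions on similar outcomes, further contributing to evidence-based practice".

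**The concern.** The Abstract promises two effects at T2, but the design supplies one comparison there. No department receives phase 1 without phase 2, and none receives phase 2 without phase 1. A difference between arms at 18 months could reflect a lasting effect of the needs assessment, an effect of the solutions, or both, and the arm comparison cannot apportion it.

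Attribution is what is at stake. The article says its results will go to the vocational education council and to policy makers. For them it matters whether the participatory process or the implemented solutions did the work. The remark about comparing solutions raises a similar problem: each school contributes a single intervention-control pair of departments, so a difference between the two schools' results need not come from their solutions.

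**Working it through.** The plan gives no figure on this point, so the check is one of identifiability.

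**Inputs**
- Conditions: two, intervention and business as usual (Methods/Design).
- Departments: one intervention and one control in each of two schools, so four (Study population).
- Occasions: T0, T1 at 6 months, T2 at 18 months (Methods/Design).
- Sequence: phase 1, then phase 2, in the same departments (The intervention; Phase 2: Implementation).

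**Step 1: count what can be estimated.** Two arms by three occasions give 2 × 3 = 6 cell means. To deliver what the Abstract promises, a model needs seven parameters: intercept, arm, T1, T2, phase 1 effect at T1, phase 1 effect at T2, and phase 2 effect at T2. The last two are both switched on in exactly one cell, intervention at T2, so their columns in the design matrix are identical. The 6 × 7 matrix has rank 6. Replacing the two T2 effects with one combined effect gives a 6 × 6 matrix of rank 6, which is fully identified.

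**Step 2: write out the contrasts.** Let P1(t) be the phase 1 effect at month t, P2 the phase 2 effect at month 18 and I any interaction. Leaving confounding aside, the baseline-corrected arm differences are:
- at T1: D1 = P1(6)
- at T2: D2 = P1(18) + P2 + I

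Subtracting, D2 − D1 = [P1(18) − P1(6)] + P2 + I. This equals the contribution of phase 2 (P2 + I) only if P1(18) = P1(6). The article neither states nor tests that. Its own Discussion says that behavioural and organizational change is slow and that both follow-ups may come too early, which makes constancy hard to take for granted.

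**Step 3: illustrate the size.** Use as a unit the vitality difference in the sample size section, 4.21 − 4.01 = 0.20 points. Assume, for illustration only, D2 = 0.20 and D1 = 0.10. Then P2 + I = 0.20 − P1(18):
- phase 1 effect has faded to 0: phase 2 contributes 0.20
- phase 1 effect constant at 0.10: phase 2 contributes 0.10
- phase 1 effect has grown to 0.20: phase 2 contributes 0

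All three give the same arm-by-time means. The split can run from none to all of the T2 effect without contradicting them.

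**Step 4: look for other routes to the split.**
- The per-protocol set is defined by phase 1 steps alone. Those workers' departments also go through phase 2, and taking part is self-selected.
- Reach (attendance in each phase and in the resulting measures) and dose received are recorded in the process evaluation. They show who took part in what, but participation was not assigned.
- Occupational and organizational efficacy, and job demands and resources, are measured and could support a pathway analysis, which would need its own assumptions.

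**Step 5: the comparison of solutions.** In each school, subtract the control department's change from the intervention department's change. Differences shared by the whole school drop out. The difference between the two schools' results then contains the difference in solutions, any school-by-intervention modification, and whatever is peculiar to the departments. With one pair per school there is no replication to separate these.

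**The case against.** The strongest reply is that the article's central question concerns the whole intervention against business as usual, which is what the T2 contrast estimates. The Methods sentence, read to its end, sets both phases against one comparator: "tailored work-oriented solutions (phase 2: implementation plan), compared to business as usual". Phase 2 grows out of phase 1, so on a total-effect reading the long-term effect of the needs assessment includes the solutions it led to. That stands for the central question. It does not rescue the Abstract, which lists the long-term phase 1 effect and the effect of the solutions as two things to be determined at T2.

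A reader might go further and infer that no data at all bear on the split. The article does not support that. Workers in one department can differ in whether they took part in phase 1, and participation, reach and mediators are measured. The evidence is weak and self-selected, but it exists.

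A reader might also infer that comparing solutions is nothing more than comparing two schools, or that a planned test has zero residual degrees of freedom. Neither holds. The within-school controls remove shared school differences, each management team may choose several solutions, and the sentence is a Discussion remark with no test attached.

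**Conclusion.** The point holds for the two separate T2 effects. The arm contrast at T2 identifies one quantity, the total programme effect including interaction, where the Abstract claims two. This is structural and independent of sample size. The T1 contrast for phase 1 and the T2 contrast for the whole programme remain estimable, subject to the non-randomised allocation and the two departments per arm.

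The conclusion rests on two readings of the text. First, there is no phase-1-only, phase-2-only or staggered group. The flow chart (Figure 2) is not shown in the text at hand, but the written description has only two conditions. Second, T1 precedes any material implementation of solutions, as the Abstract's T1 aim implies.

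The defect lies in a stated aim and a Discussion remark. The outcomes, planned models and data collection are not at fault, but what may be concluded at T2 changes.

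**What to change.** 1. In the Abstract and Methods/Design, state T1 as the effect of phase 1 and T2 as the effect of the combined two-phase programme, each versus business as usual. Drop the promise of two separate effects at T2.
2. If a split by phase is still wanted at T2, label it exploratory and state its assumptions: constancy of the phase 1 effect from month 6 to month 18 for T2 minus T1, and the self-selected nature of the data for analyses using participation, reach or mediators.
3. In the Discussion, present the school-specific solutions descriptively alongside the process evaluation. Say that with one intervention-control pair per school, differences between solutions cannot be separated from school-by-intervention and department differences.

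The cost is wording only. No measurement, sample size or planned model has to change.

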**Discussion:**

“Bottom-up Innovation” is a combined effort of the educational sector, intervention providers and researchers. Results will provide insight into (1) the relation between participating in the intervention and occupational and organizational self-efficacy, (2) how an improved balance between job demands and job resources might affect need for recovery and vitality, in the short and long term, from an organizational perspective, and (3) success and fail factors for implementation of an organizational intervention.

**Trial registration number:**

Netherlands Trial Register NTR3284

## Background

The Dutch government aspires a top five position in the global rankings for education and science [1], to ensure the competitive power of the Dutch economy. Improving the educational quality is crucial to achieve this ambition. Undisputedly, teachers and their managers play an important role in maintaining and improving the quality of education [2]. However, almost one in five workers in the Dutch educational sector (18%) suffers from work-related stress complaints, compared to one in eight workers in the Dutch working population (13%) [3]. Work-related stress is an important cause for mental health problems, such as burnout. Burnout is associated with reduced work performance (e.g. [4,5]) and its high prevalence in the educational sector thus interferes with the Dutch government’s ambition.

### Work-related stress as a major problem

Burnout, as an ultimate outcome of work-related stress, is considered a prolonged response to chronic emotional and interpersonal stressors in the work context, characterized by emotional exhaustion, depersonalization and reduced personal accomplishment [6]. The work context comprises two specific sets of characteristics that influence burnout and well-being: job demands and job resources. Job demands are generally considered the physical, social or organizational aspects of the job that require sustained physical or psychological effort [7]. Job resources are the physical, social or organizational aspects of the job that may reduce job demands, help to achieve goals and stimulate learning and development [7]. A job demand, such as dealing with students with special needs, will turn into a stressor over time if job resources, such as coworker support, are insufficient or lacking [8,9]. In the educational sector job demands have intensified at rapid pace [10], while job resources remained the same. For example, the student-teacher ratio has increased [11]; students with special needs have been integrated in the regular classes [12]; the number of accountability measures has grown, leading to numerous administrative tasks and consequent paperwork [13]; and several school reforms have been implemented in the educational sector, often even overlapping [14]. It seems likely that this intensification of job demands has contributed to the current burnout rates.

### Consequences of work-related stress

Work-related stress may show as decreased vitality and increased need for recovery. These precursors of burnout have been associated with several other negative organizational outcomes, for example sickness absence and retention problems. First, sickness absence rates are relatively high in the educational sector [3]. More often than in other sectors, workers in education consider their absence a result of emotionally demanding and stressful work [3]. If a teacher falls ill, the work is often temporarily accounted for by his or her colleagues, thereby increasing the workload (i.e. a job demand) for this colleague while job resources remain the same. This practice, although not in line with sickness replacement regulations in Dutch schools, disturbs the equilibrium between job demands and job resources of healthy colleagues. Second, a large number of teachers retire before reaching the official retirement age [15]. Between 45% [16] and 70% [17] of early retirements in teachers is accounted for by psychosomatic illness and psychological problems. Furthermore, approximately half of all novice teachers leave the sector within their first five years, as noted in a North American study [18]. Retention of both novice and experienced teachers is thus a challenge with societal implications. Burnout rates, sickness absence and lower retention rates sum up to a reduced employability of the work force, which is costly. In The Netherlands alone, work days lost due to presenteeism and sickness absence associated with mental health problems summed up to 2.7 billion Euros in 2008 [19,20]. There is thus an urgent need for stress management interventions in the workplace. Ideally these interventions alter precursors of burnout, such as need for recovery and reduced vitality.

### Interventions in education: individual-focused and secondary preventive

Stress management interventions can be classified as primary, secondary or tertiary prevention. Primary preventive interventions aim to alter the sources of stress at work (e.g. [21]). Secondary preventive interventions aim to reduce stress symptoms before they lead to health problems (e.g. [21]). Tertiary preventive interventions aim to treat health problems (e.g. [22]). Giga, Cooper and Faragher [23] found that most common stress management interventions are ‘secondary preventive’, aimed at the individual level and comprised stress management and coping techniques. The same holds true for stress management interventions in the educational sector. Until now stress management interventions in education have been ‘secondary preventive’ mostly and targeted at the individual level [24-28]. These interventions [24-28] all aimed to enhance the individual capacity of (trainee) teachers or teaching assistants to cope with stressors in the workplace, for example via mindfulness-based stress reduction or workshops on stress management skills. However, these interventions were only partly effective in influencing (dimensions of) burnout [24-28] and well-being [28]. More specifically, none of the studies influenced all three burnout dimensions positively, some influenced two dimensions (but always in differing combinations) and the long term effects were not measured. Apparently it is insufficient to reduce burnout and increase well-being in education, by focusing solely on strengthening the individual teachers’ capacity to cope with or manage stress.

### The need for primary preventive organizational interventions and appropriate evaluation studies

The above leads us to the proposition that to decrease (precursors of) burnout, problems should be altered at the source, that is the (interpersonal) work context [8,29], and targeted at the organizational level. This proposition is amplified firstly by the enormous body of research that points to the importance of the (interpersonal) work context in the development of a disbalance between demands and resources (e.g. [30,31]).

Secondly, McVicar, Munn-Giddings, & Seebohm [32] found that primary preventive interventions can take the complexity of an organization into account when designing a preventive strategy. These interventions are therefore potentially more effective than individual level interventions [32].

A review has suggested that if an intervention is effective, the organizational level ones are more likely to bring about positive changes than the individual level ones [33]. On the other hand, two meta-analyses on stress management interventions have failed to show substantial effects of organizational level interventions over individual level interventions [34,35], but this has partly been explained by the underrepresentation of organizational outcome evaluation [35]. For another part, it might be explained by the finding that 'organizational-level occupational interventions are often complex programs involving many people and several intervention components, which might […] complicate the implementation process and the measurement of effects’ ([36], p.85). These interventions thus impose specific demands on the design of the evaluation study (e.g. monitoring the implementation process), demands that cannot be fulfilled by the gold standard design for experiments: the randomized controlled trial [37]. An organization is no laboratory where all conditions can be controlled. However, Griffiths [38] points out that occupational health interventions are still mostly regarded as experiments, set up to discover whether changes occur after manipulating a variable or introducing a particular treatment. Experiments focus on *what* works, thereby discarding to describe the processes which brought about these outcomes (*how* and *why* does it work?) [37]. Nielsen and colleagues [37] posed, that there is a lack of interventions that combine process measures (e.g. managerial support for the intervention) and effect measures (e.g. job demands). To further understand the ‘black box’ and increase the external validity (or generalizability) of interventions, the intervention ought to be evaluated by means of mixed methods [37].

The above underlines the need for appropriate evaluation of primary preventive organizational interventions. This implies for the evaluation study in the current project that: 1) the evaluation design is as rigorous as possible, 2) the implementation process is monitored by assessing process variables, 3) in the analyses it will be assessed how process variables influence intervention outcomes, and 4) (objective) organizational outcomes are measured.

